## Methods

### Trial design

The AUTHARK study is designed as an interventional randomized controlled study with two parallel treatment arms.

Figure 1 shows the overall design of the AUTHARK study. After the initial screening at T1, patients who meet the inclusion criteria will be randomly assigned to one of the treatment arms. Children in both the experimental group and the control group will receive social skills training (combination of THAV [4] and ScouT [7]). In addition to the treatment, the AUHARK smartphone app will be used in the experimental group. The treatment will be administered in three phases (1–3). Each phase includes eight weekly therapy sessions with the children and two to three sessions with the parents/caregivers. The first treatment phase (1) is followed by an intermediate assessment (T2) with a reduced set of assessment instruments. The second treatment phase (2) is followed by a major assessment (T3). Children who no longer show clinically significant symptoms of ODD/CD at T3 will not receive further therapy but will participate in a first follow-up assessment (T4) eight weeks after T3. Those patients with significant symptoms at T3 will undergo a third treatment phase with a further eight child sessions and two to three caregiver sessions, which will be followed by the T4 assessment. A follow-up evaluation (T5) for all patients will take place one year after T4.

**Fig. 1 Fig1:**
[figure not shown]
Overall design of the AUTHARK study

### Study setting

The AUTHARK trial is a single-center study located at the School for Child and Adolescent Cognitive Behaviour Therapy (AKiP), Faculty of Medicine and University Hospital Cologne, University of Cologne.

### Recruitment, inclusion and exclusion criteria

Patients for the AUTHARK study will be recruited from three different sites: (1) the outpatient units of the Department of Child and Adolescent Psychiatry and of the School of Child and Adolescent Behaviour Therapy (AKiP) at the University Hospital Cologne, (2) primary and special education schools and (3) pediatric and psychiatric practices in Cologne, Germany.

Participants will be included if they meet the following inclusion criteria: (1) child age: 6;0 to 12;11 years at T1; (2) clinician-rated diagnosis of ODD/CD based on a structured interview (ILF-EXTERNAL) that is part of the comprehensive Structured Interview for Children and Adolescents according to ICD-10 and DSM-5 from the DISYPS Systems (DISYPS- ILF) [53] at T1; (3) parent-rated ODD/CD symptoms from the parent-rated DISYPS III Symptom Checklist for Disruptive Behaviour Disorder (SCL-DBD parent) [43] with a stanine score of 7 or higher at T1; (4) peer-related aggressive (verbal and/or physical) behavior must be reported by the parents/caregivers at T1; (5) willingness and ability (e.g. sufficient knowledge of German, sufficient competence in using a smartphone) of patient and parents/caregivers to participate in the intervention; (6) children treated with a stable dose of psychotropic medication (e.g. methylphenidate) will be included in the trial. Criteria (2) and (3) will also be evaluated again at T3. If these two criteria no longer apply to the patients at T3, the study participation will be terminated.

The following exclusion criteria will be applied and evaluated at T1: (1) child’s intelligence is below average (IQ < 85) based on a standard intelligence test (German version of the Culture Fair Intelligence Test, Primary Intelligence Scale 1 (CFT 1-R) [54] and Scale 2 (CFT 20-R) [55]; (2) Autism spectrum disorder or other severe comorbid disorder which dominates the clinical picture according to clinical rating; (3) Current or planned inpatient psychotherapy or outpatient behavioral parent management training on a weekly/biweekly basis; (4) Low level of German language skills of the patient or the parents/caregivers.

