#### Participant timeline

The individual study duration per patient is between five and seven months. Measurements will take place according to a specific schedule. The trial consists of three general parts: a screening process, the intervention period, and the follow-up assessment. Through an initial investigation using standardized telephone screening, a broad assessment of the inclusion and exclusion criteria will be conducted. Shortly after this initial investigation, the pre-treatment measurement (T1) will occur, which involves a detailed examination of the inclusion and exclusion criteria. After being randomized to the experimental or control group, all patients will undergo a first treatment phase (1), consisting of eight patient sessions and two to three parent/caregiver sessions, followed by an intermediate assessment (T2). Subsequently, another treatment phase (2) will be carried out, followed by a main assessment (T3). Non-responders to the treatment (significant symptoms of OD/CDD at T3 based on the clinician-rated parent interview (ILF-EXTERNAL) [53] and on the parent rating (SCL-DBD) from the DISYPS-III [43]) will participate in a third treatment phase (3), followed by a final assessment (T4). Responders to the treatment (no significant symptoms of ODD/CD at T3) will terminate the study and take part in a first follow-up assessment (T3) eight weeks after their last session. After one year, every family will be asked to complete a follow-up survey (T5).

Therefore, four study visits (T1-T4) will take place for all children and parents/caregivers in order to complete assessments. Additionally, there will be 16 study visits for all children and four to six study visits for all parents/caregivers (treatment phases 1 and 2). Within the group of non-responders after T3, there will be a further eight visits for children and two to three visits for parents/caregivers (treatment phase 3).

At the main assessment points (T1, T3/T4), the primary outcome (THA) and the secondary outcomes will be assessed. At the intermediate assessment (T2), the primary outcome and symptoms of ODD/CD as well as comorbid conditions will be assessed using only parent- and child-report questionnaires and without a clinical interview. The primary outcome will additionally be assessed every two weeks, as the therapist will rate the children’s THA using the Adherence Questionnaire (Fig. 5).

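### The eligibility section ends study participation for children who have remitted at T3, while the rest of the protocol keeps them for T4 and T5: a minor wording error to correct

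*Protocol article*

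**What the plan says.** Four places in the Protocol article deal with what happens to a child who has improved by T3.

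- **Recruitment, inclusion and exclusion criteria.** Criterion (2), the clinician-rated ODD/CD diagnosis from the ILF-EXTERNAL interview, and criterion (3), a parent-rated SCL-DBD stanine of at least 7, are checked again at T3. Then: "If these two criteria no longer apply to the patients at T3, the study participation will be terminated".
- **Trial design.** Children without clinically significant ODD/CD symptoms at T3 "will not receive further therapy but will participate in a first follow-up assessment (T4) eight weeks after T3". It adds: "A follow-up evaluation (T5) for all patients will take place one year after T4".
- **Participant timeline.** Responders, defined by the same interview and the same parent scale, "will terminate the study and take part in a first follow-up assessment (T3) eight weeks after their last session". The same section says that "four study visits (T1-T4) will take place for all children and parents/caregivers in order to complete assessments" and that each family is asked for the T5 survey a year later.
- **Missing values.** Patients are to remain under follow-up and documentation once treatment has stopped, so that the data needed for the intention-to-treat principle are recorded.

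**The concern.** The children addressed by the eligibility sentence are the timeline's responders, because both sections use the same two instruments. A child whose participation has ended cannot also be due for two further assessments, so staff cannot follow both instructions as written. The timeline does not settle the matter. It repeats the idea of leaving the study, schedules a visit afterwards, and gives that visit a label that already belongs to the assessment at which response is judged.

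If the eligibility sentence were applied literally, the children removed from T4 and T5 would be exactly those who had improved. That is selection on an outcome observed after randomization. Hypothesis 2 expects symptoms to fall more in the app group. If response did differ by arm, the children remaining at T4 and T5 would no longer form randomized groups. Two uses of the data would suffer: the analysis of predictors and moderators of outcome at T4, and the one-year follow-up, which would then describe non-responders only.

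**Working it through.** No sample-size, power or alpha figure is involved. The main check sets the texts side by side for a responder.

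| Section | Therapy after T3 | T4 | T5 |
|---|---|---|---|
| Recruitment, inclusion and exclusion criteria | none (participation over) | no | no |
| Trial design | none | yes, 8 weeks after T3 | yes, all patients |
| Participant timeline | none (said to leave the study) | yes: an 8-week follow-up labelled T3, and T1 to T4 for all children | yes, every family |
| Missing values | (not addressed) | follow-up continues after treatment | follow-up continues after treatment |

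The eligibility section stands alone. The Missing values sentence is written mainly with premature stopping in mind. Even so, a plan that keeps early leavers under observation would hardly mean to release children who completed treatment and did well.

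**Assessments at stake.** The schedule has five, T1 to T5. Under the literal reading a responder loses T4 and T5, which is 2 of 5.

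**Primary endpoint.** The section on its analysis uses T1, T2, T3 and the session-level scores. All of these come no later than the T3 decision, so nothing is lost.

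**Duration as a side check.** The timeline states: "The individual study duration per patient is between five and seven months". The Trial design section states: "Each phase includes eight weekly therapy sessions with the children". Months = weeks × 7 / 30.44.

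- Responder leaving at T3: 2 × 8 = 16 weeks; 112 / 30.44 = 3.7 months, below the stated range.
- Responder staying to T4: 16 + 8 = 24 weeks; 168 / 30.44 = 5.5 months, inside it.
- Child with a third phase: 3 × 8 = 24 weeks = 5.5 months, inside it.

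The stated range therefore fits responders staying to T4. The check assumes an unbroken weekly pace. Five months is 5 × 30.44 / 7 = 21.7 weeks, so about 21.7 − 16 = 5.7 weeks of breaks and assessment intervals would bring even a child leaving at T3 up to the lower limit. It is weak support, and it says nothing about T5.

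**The case against.** The strongest reply is that this is loose wording and nobody would be misled. The timeline has responders leaving the study and attending a follow-up in the same sentence, so the authors evidently use such phrases for leaving the treatment course. The Interventions section likewise counts the duration of the trial in therapy sessions, and the stated study duration of five to seven months cannot include T5. The schedule for responders is spelled out in two sections, and the conflicting rule is one closing sentence elsewhere.

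Much of this stands. End of treatment is the probable intent, and the harm described above is conditional on a literal reading. What does not stand is that no correction is needed. The sentence is an operative rule about study participation, and it cannot be followed together with the schedule.

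A reader might infer more than the documents support:

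- *That the trial plans to drop its responders.* It does not; the Trial design and Participant timeline sections schedule them for T4 and T5.
- *That the primary comparison is biased.* It uses data up to T3 only.
- *That the secondary outcomes lose their post-treatment value.* They are assessed at T1 and at T3 or T4, which may simply mean the end of each child's treatment.
- *That the individual stopping rules disprove the eligibility sentence because response is not among the listed reasons.* That list concerns children counted as dropouts. A child who completes the planned 16 sessions is not one, so the omission proves little.

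**Conclusion.** The eligibility sentence is wrong as written, and the severity is minor. It contradicts the Trial design, Participant timeline and Missing values sections. The timeline has two slips of its own: the statement that responders leave the study, and the label T3 on what must be T4. The contradiction rests on the text alone and does not need the duration arithmetic.

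The consequence is conditional. If the sentence were applied literally, each responder would lose 2 of 5 assessments, and the T4 predictor and moderator analysis and the one-year follow-up would be restricted to children who had not improved. The primary endpoint is unaffected. The article gives no T3 response rate, so neither the number of children nor the size of any bias can be derived. The intended design can be recovered from the other sections, so this corrects the wording and does not criticise the design.

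**What to change.** Make three changes of wording:

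1. In the section on recruitment, inclusion and exclusion criteria, replace the consequence stated for children who no longer meet criteria (2) and (3) at T3 with: *treatment will end, and the child will continue to the T4 and T5 assessments*.
2. In the Participant timeline, replace the statement that responders leave the study with: *will end treatment*.
3. In that same sentence, change the label of the eight-week follow-up from T3 to T4.

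The change should cover T3 responders only, with the individual stopping rules left in force. A broader promise to continue T4 and T5 for every randomized child unless consent or assent is withdrawn would create a new conflict, because those rules also end participation for unwillingness to continue, for inpatient need or other reasons of well-being, and for need of a different treatment.

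The cost is a wording amendment; T4 and T5 are already scheduled. Recruitment began in October 2019, so many children had probably passed T3 when this protocol version was issued in April 2022. The change was still of use then. With recruitment planned to finish in May 2022 and five to seven months per child, the last T4 visits would fall around October to December 2022 and the last T5 about a year later.

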### Allocation

Participants will be randomly assigned to either the treatment condition including the AUTHARK app [56] (*n* = 35) or the active control condition, which includes treatment without the AUTHARK app but with paper-and-pencil homework assignments (*n* = 35). We will use computerized block randomization with a block size of 4 and random selections from all 6 permutations. Allocation will only take place after the participants have completed the initial screening, fulfilled all the inclusion criteria and gave their written consent (patients, parents and teachers). The participants will be randomized by the Principal Investigator [name]. The staff members who are also responsible for the recruitment and the initial diagnostics will request randomization. In return, [name] will send a digital answer form to the same staff member, containing the group allocation (experimental or control group). The staff member will then inform the therapist and the family about the treatment intervention.

Due to the nature of the intervention, it will not be possible to blind trial participants, parents/caregivers, and therapists to allocation. However, the parents/caregivers and patients will be blind regarding the specific hypotheses.

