#### Sample size

A total number of 70 children 35 / 35 between the ages of 6;0 and 12;11 will be included in this exploratory study. To date, the effects of smartphone-augmented CBT on the implementation of therapy homework in children with aggressive behavior have barely been investigated. Other explanatory studies refer to an even a smaller number of cases [15, 23]. As the AUTHARK study aims to provide a basis for preparing a subsequent multicenter trial, the sample size needed is not based on formal power calculations. Instead, a sample size is proposed that allows us to precisely estimate the variance of critical outcome parameters that can then be entered into a power calculation for a confirmatory trial. In this way, the overall sample size for the main RCT can be minimized [74].

Based on results from the previous literature, we assume a small to moderate effect size (Cohen’s d ~ 0.4) [75], for which approximately 30 participants per treatment arm for a pilot randomized trial are recommended [74, 76]. Furthermore, a study with a similar design, comparing two groups across four assessment points (pre-, post-, and follow-up measurements), expects moderate effects regarding the app’s influence on therapy homework with a sample size of *n* = 35 per group [16]. Moreover, the power of a sample can be increased by a high number of measurements per patient [77]. In our study, THA will be measured at least eight times over a period of approximately sixteen weeks. At each assessment, the patients will be asked to use the smartphone app for five consecutive schooldays. Based on previous trials with a similar patient population and interventions, a dropout rate between 10 and 15% is expected [78]. Therefore, *n* = 35 patients per group (total: *n* = 70) should be recruited.

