### Trial status

#### Protocol version: 01 / 2022, issue date: 06.04.2022

The recruitment for the AUTHARK study has already started in October 2019 and is still ongoing by the time of the submission of this protocol. The completion of recruitment is planned for May 2022. Due to the Covid-19 pandemic and its various challenges regarding ongoing research projects, this paper could not be finalized and submitted earlier.

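### Fixed blocks of 4, with each allocation returned to the recruiting staff in an open single-centre trial, leave an avoidable route to selection bias

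*Protocol article*

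**What the plan says.** The Allocation section of the protocol article fixes the method: "We will use computerized block randomization with a block size of 4 and random selections from all 6 permutations". It then sets out who does what. "The staff members who are also responsible for the recruitment and the initial diagnostics will request randomization". The Principal Investigator randomizes and "will send a digital answer form to the same staff member, containing the group allocation"; that person then informs the therapist and the family. The same section says that "it will not be possible to blind trial participants, parents/caregivers, and therapists to allocation".

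Two safeguards are stated there. Allocation comes only after screening, fulfilled inclusion criteria and written consent, and the person who randomizes is not the person who asks.

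Under Study setting: "The AUTHARK trial is a single-center study located at the School for Child and Adolescent Cognitive Behaviour Therapy (AKiP"). Under Sample size: "A total number of 70 children 35 / 35 between the ages of 6;0 and 12;11 will be included in this exploratory study". Under Trial status, recruitment began in October 2019 and was still open at submission: "The completion of recruitment is planned for May 2022".

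**The concern.** With a constant block of 4, two app and two control places must appear in every four allocations. Someone who knows the block size and the tally so far knows the last arm of each block, and sometimes the third. The recruiting staff are the people to whom allocations are returned, and treatment is open, so little in the described procedure keeps the tally from them.

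A prediction matters only if there is room to act on it. Among the eligibility criteria, several rest on judgement: willingness and ability to take part, competence with a smartphone, sufficient German, and whether a comorbid disorder dominates the clinical picture. These are settled before allocation, when the next arm may already be predictable.

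The primary outcome is homework adherence, and the abstract names lack of motivation as an obstacle to it. If more motivated or smartphone-competent families were enrolled when the app was the likely next arm, part of any difference in adherence would come from selection. Baseline data would show this poorly, because homework is first assigned at session 2 and no homework record exists before treatment.

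**Working it through.** **Inputs.** Block size 4, 1:1, 6 permutations (Allocation); N = 70, 35 per arm (Sample size); one centre (Study setting). Assumptions: one running list, and an observer who knows the block size and all earlier allocations.

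**The plan's own figure.** The number of ways to place two app slots among four is C(4,2) = 6, as stated.

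**Predictability by position.** An arm is certain when the other has used both its places. The best guess is the arm with more places left. The first two allocations match in 2 of 6 permutations (1/3). The third is then certain; otherwise it is even. So the guess at position 3 is right with probability 1/3 × 1 + 2/3 × 1/2 = 2/3.

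| Position | P(certain) | P(best guess right) |
|---|---|---|
| 1 | 0 | 1/2 |
| 2 | 0 | 2/3 |
| 3 | 1/3 | 2/3 |
| 4 | 1 | 1 |
| Mean | (4/3)/4 = 33.3% | (17/6)/4 = 70.8% |

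**At N = 70.** There are 17 full blocks and two positions of an 18th.

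- Certain: 17 × 4/3 + 0 = 22.7, and 22.7/70 = 32.4%.
- Correct guesses: 17 × 17/6 + (1/2 + 2/3) = 48.17 + 1.17 = 49.3, and 49.3/70 = 70.5%. With no predictability the rate is 50%.

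**What other block sizes would give.** Fixed sizes are enumerated exactly per full block. Mixed sizes are simulated (3,000 runs, N = 70) with an observer who knows the possible sizes but not which one is in use. The same simulation with size 4 returns 32.4% and 70.5%, matching the exact values.

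| Scheme | Certain | Best guess right |
|---|---|---|
| Fixed 6 | 25.0% | 68.3% |
| Fixed 8 | 20.0% | 66.6% |
| Mixed 4, 6 | 5.5% | 69.1% |
| Mixed 2, 4, 6 | 4.0% | 70.1% |
| Mixed 4, 6, 8 | 2.3% | 67.8% |

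**What steering could do (illustration only).** Suppose a recruiter enrolled families shifted by +δ SD in adherence tendency whenever the app was likelier, by −δ when control was likelier, and by nothing when even. Correct minus wrong guesses per block is 0 + 1/3 + 1/3 + 1 = 5/3. Dividing by two children per arm gives an expected bias of 0.83δ. The documents give no δ. For an assumed δ of 0.1 to 0.3 the bias is 0.08 to 0.25 SD, or 21% to 63% of the d of about 0.4 in the Sample size section. This presumes full knowledge and action at every chance.

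**The case against.** A reader might infer that recruiters knew a third of the assignments, or that the sample was in fact selected. The documents support neither. Certainty needs one person to hold both the block size and the whole sequence. The article does not say that recruiters knew the block size. It speaks of staff members in the plural, each answered on their own request. It is dated 8 July 2022, after the planned end of recruitment, so on that plan publication did not disclose the block size during enrolment. A single unstratified list is also an inference from silence.

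The room to act is limited as well. Age, the structured interview, the stanine threshold and the IQ test rest on instruments. With 70 children over about 31 months (October 2019 to May 2022), or about 2.3 a month, there is little scope for reordering families to fit a slot.

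The remedies have limits too. Mixed blocks barely lower the best-guess rate. With recruitment due to end in May 2022, a new list reaches few children. SCL-DBD and age do not measure motivation or smartphone competence. Covariates and sensitivity analyses may be left to the analysis plan, so their absence from the article is not a fault.

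All of this stands and reduces the size of the concern. It does not remove it. Allocating after consent prevents reaction to a known allocation, not prediction of the next one. In an open single-centre trial results are easily shared, and nothing described prevents that. The block-history covariate also answers the objection about unmeasured traits, because selection by prediction acts through that probability whatever trait was used.

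**Conclusion.** The point holds as a weakness in a stated procedure. Given one running list and an observer with the block size and full history, about 22.7 of 70 assignments (32.4%) are knowable in advance and about 49.3 of 70 (70.5%) can be guessed correctly. The stated safeguards and the instrument-based criteria make the practical risk smaller than those figures suggest. Whether anyone had the knowledge, or used it, cannot be told from the article. Late recruitment limits a change to the list but not a change to the analysis, which needs only the allocation order and T1 data. It is a cheap improvement worth making, not a flaw that invalidates the trial.

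**What to change.** 1. **Allocations still to be made.** Use randomly varying block sizes, do not disclose them to recruiters, and keep the running sequence from recruiting staff. Both parts are needed: sizes of 2, 4 and 6 cut certain assignments to about 4% but leave the best-guess rate near 70%. Cost: a setting in the list generator, a change in who receives the result, and a slightly larger possible imbalance between arms.
2. **Children already randomized.** Adjust the primary homework-adherence model for T1 parent-rated SCL-DBD and child age. Prespecify a sensitivity analysis that adds each child's probability of app assignment given the block history (0, 1/3, 1/2, 2/3 or 1). Compare baseline characteristics between arms by predictable and unpredictable position, as description only.
3. **Reporting.** State who knew the block size and who could see the sequence.

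The adjustment costs a few degrees of freedom. The sensitivity analysis also loses precision. The mean of p(1 − p) per block is (1/4 + 2/9 + 1/6 + 0)/4 = 0.160, against 0.25 without the covariate, so the standard error of the group effect grows by about √(0.25/0.160) = 1.25, to a first approximation. With 70 children, about 23 of them in certain positions, the check has low power, and a null result is not proof that no selection took place.
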